## Description of protocol

### Overview

This protocol employs a laboratory-based, randomized within-subject crossover experimental design to examine the associations between contagious yawning stimuli exposure and subjective and physiological indicators of sleepiness. The protocol follows a 2 × 2 factorial structure manipulating: (1) stimulus type (human vs. digital character yawning) and (2) auditory content (with vs. without sound), yielding four experimental conditions.

Participants complete two sessions on separate days. In one session, they view human yawning videos under both auditory conditions in randomized order. In the other session, they view yawning videos of digital characters under the same auditory conditions. The order of sessions (human first vs. digital first) will be counterbalanced across participants. The order of conditions will be randomized and counterbalanced to minimize systematic order effects.

A within-subject design was selected to maximize sensitivity to condition-related differences while controlling for interindividual variability in baseline sleepiness, circadian preference, and autonomic functioning. To mitigate potential fatigue or habituation effects, experimental sessions will be conducted on separate days with a minimum interval of one-day between sessions.

The protocol is designed to examine relative differences across yawning stimulus conditions and within-subject changes over time, rather than to isolate yawning-specific causal effects relative to neutral stimulus exposure. Accordingly, non-yawning control conditions are not included. This design enables focused comparison across stimulus modalities and representations while maintaining a manageable experimental duration within a multimodal physiological recording context, which is consistent with prior studies using contagious yawning stimuli [26,27]. Pre-stimulus baseline recordings will be obtained prior to each condition, which allows within-subject quantification of changes relative to a stable resting reference.

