Finally, a video camera will be positioned to capture the participant’s facial expressions throughout the session. The camera angle will be adjusted to ensure a clear view of the face, and ambient lighting will be optimized to support subsequent behavioral coding. A brief test recording will be conducted to confirm that facial features are clearly visible.

To ensure consistency across participants, the experimental environment will be standardized. Room temperature will be maintained between 20 and 22 °C throughout the session. Lighting conditions will be controlled at a moderate and consistent level. External noise and potential interruptions will be minimized as much as possible. Participants will be seated comfortably in a chair with back support, and the display screen will be positioned at eye level and at an appropriate viewing distance to reduce physical strain.

Following equipment setup, a five-minute baseline physiological recording will be conducted. This duration was selected based on prior studies examining the signal lengths required to reliably derive downstream physiological and cognitive indices [[37], [38], [39]]. Participants will be instructed to sit quietly in a reclining chair and relax while maintaining their gaze on a neutral fixation point displayed on the screen. All physiological signals will be recorded continuously during this period. To avoid introducing confounding influences, no conversation or additional instructions will be provided during the baseline recording.

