#### Experimental procedure

Each experimental session includes two yawning stimulus conditions (with sound and without sound) presented in randomized, counterbalanced order. To minimize social presence effects on yawning responses [40,23], participants will remain alone in the experimental room throughout stimulus presentation, while the experimenter monitors the session remotely from an adjacent space via a live physiological data feed and video stream.

At the beginning of each condition, physiological recording will begin continuously, and participants will be instructed to watch the videos naturally and to maintain a comfortable and relaxed posture. No further instructions regarding yawning will be given at this stage, as participants will have been informed of their freedom to respond naturally at the pre-session assessment stage.

Stimulus presentation will then proceed for approximately 5 min. Each stimulus sequence will consist of approximately 50 discrete yawning events, each approximately 6 s in duration [41,42]. This duration is consistent with prior experimental yawning paradigms in contagious yawning research and falls within the commonly used 3–5 min exposure range [15,22]. During this period, all physiological signals will continue to be recorded continuously, and participant behavior will be monitored via the video recording. Particular attention will be given to signs of sleep onset such as sustained eye closure. If sleep onset occurs, the corresponding timestamp will be noted, and recording will continue without interruption.

Following stimulus presentation, a post-condition assessment period of approximately 10 min will be conducted. Video will be stopped, and subjective sleepiness will be assessed using the KSS. Participants will also complete a brief questionnaire regarding their yawning behavior, including whether they yawned or experienced an urge to yawn [40].

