After the first condition, a standardized wakefulness reset period of approximately 15 min will be implemented. During this period, laboratory lighting will be increased, and participants will be encouraged to engage in light activities such as standing, brief walking, or casual movement. These activities are intended to promote wakefulness without inducing excessive physical exertion. Intentional or exaggerated upper-body stretching will not be encouraged, in order to minimize potential facilitation of yawning behaviour. Light conversation may be used when necessary to reduce accumulated sleep pressure. At the end of the reset period, subjective sleepiness will again be assessed using the KSS to confirm that participants have returned to an adequate level of alertness. If participants continue to exhibit signs of drowsiness, the reset period may be extended, or additional light activities may be introduced before proceeding.

The second condition will then follow the same procedure as described above. Upon the completion of both conditions (with and without sound), all physiological sensing equipment will be removed.

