#### Data pre-processing

Physiological and behavioral data will be time-aligned across sensing modalities using synchronized timestamps. For each yawning condition, physiological signals will be segmented into predefined analysis windows relative to stimulus onset.

Artifact removal will then be performed separately for each sensing modality. For wristband-based signals, visual inspection and accelerometer data will be used to identify motion artifacts, signal dropout, and periods of excessive movement, which will be excluded from further analysis. For eye-tracking data, periods of sustained eye closure indicative of potential sleep onset as well as poor-quality pupil measurements, will be excluded. For fNIRS data, standard preprocessing procedures including bandpass filtering and motion artifact correction will be applied, followed by the removal of segments affected by low signal quality. Raw optical signals will subsequently be converted into HbO_2_ and HHb concentration changes.

To ensure that analyses capture stimulus-related physiological responses rather than transitions into sleep, only data recorded prior to identified sleep onset will be included in confirmatory analyses. Data segments affected by excessive artifacts, signal loss, or sustained eye closure will be excluded from primary analyses. Baseline correction will be applied to all physiological measures to account for inter-individual differences in resting physiological states. Baseline values will be calculated for each participant using pre-stimulus periods and subtracted from condition-specific values or expressed as percentage changes, as appropriate.

Following signal cleaning, physiological features will be extracted for each experimental condition. BVP will be used to compute mean heart rate and HRV metrics, including SDNN, RMSSD, and frequency-domain measures. EDA data will be analyzed to derive tonic skin conductance level and phasic skin conductance responses. Pupil data will be used to calculate mean pupil diameter, pupil diameter variability and pupillary unrest index (PUI). Skin temperature data will be summarized using mean peripheral temperature and changes relative to baseline. For fNIRS data, temporal patterns of cortical oxygenation changes will be extracted. Finally, descriptive statistics will be used to summarize participant characteristics, baseline sleep measures, and data completeness.

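### A physiological baseline is promised before each condition, but the procedure describes one per session, taken before the wakefulness reset, and the analysis text does not say which baseline each condition uses

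*Protocol article*

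**What the plan says.** Four places in the protocol article bear on the physiological baseline.

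- **Overview.** "Pre-stimulus baseline recordings will be obtained prior to each condition". The section presents these recordings as the stable resting reference for within-subject change, directly after explaining that there is no non-yawning control.
- **Equipment and environment setup.** "Following equipment setup, a five-minute baseline physiological recording will be conducted". The participant rests and looks at a fixation point. This is the only resting recording whose length and conditions are described.
- **Experimental procedure.** Each condition opens as follows: "At the beginning of each condition, physiological recording will begin continuously, and participants will be instructed to watch the videos naturally". Then: "Stimulus presentation will then proceed for approximately 5 min". Afterwards "a post-condition assessment period of approximately 10 min will be conducted". A reset of about 15 min follows the first condition: "During this period, laboratory lighting will be increased, and participants will be encouraged to engage in light activities such as standing, brief walking". It ends with a KSS rating and may be extended. The second condition is then said to repeat the procedure already described.
- **Data pre-processing.** "Baseline values will be calculated for each participant using pre-stimulus periods and subtracted from condition-specific values or expressed as percentage changes, as appropriate".

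Table 2 says that the secondary (physiological) analyses focus on changes relative to baseline. Its fixed effects are stimulus type, sound and their interaction.

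**The concern.** The Overview and the procedure do not describe the same recordings. By the Overview there are two baselines per session and four per participant. By the procedure there is one per session. An experimenter working from the procedure would take one, and a resting period that was never recorded cannot be recovered in the analysis.

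The baseline carries more weight here than in most crossover studies. With no neutral condition, the first research question (whether human yawning videos are associated with sleepiness-related responses) has no comparator on the physiological side except the resting reference. If the second condition is compared with a rest period from before the reset, heart rate, electrodermal activity, skin temperature and pupil size may still reflect standing, walking and brighter light. That residue would be counted as response to the clips, and change from baseline would mean one thing in the first condition and another in the second.

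**Working it through.** The article states no figure on this point to reproduce. The check sets the passages side by side, adds up the timeline, and illustrates the consequence.

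**1. Is a second baseline described?** The five-minute rest belongs to equipment setup. Sensors come off only after both conditions, so setup happens once per session. The steps listed for a condition run from the start of recording and the viewing instruction to the stimulus, with no resting period. The reset ends with a KSS only. The instruction to repeat the procedure sits under Experimental procedure, whose steps contain no baseline. The natural reading is one baseline per session, against two in the Overview.

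**2. Does the analysis text settle it?** No. Data pre-processing speaks of values for each participant from pre-stimulus periods, both in the plural. That fits a participant, session or condition baseline.

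**3. How old is the session baseline when each condition starts?** Inputs: stimulus about 5 min, post-condition assessment about 10 min, reset about 15 min.
- First condition: it follows directly.
- Second condition: 5 + 10 + 15 = 30 min, longer if the reset is extended.

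**4. Does session length show which was meant?**
- One baseline: 5 + (5 + 10) + 15 + (5 + 10) = 50 min, leaving 70 − 50 = 20 min.
- Two baselines: 50 + 5 = 55 min, leaving 70 − 55 = 15 min.

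Both fit, so the length neither requires nor rules out a second baseline.

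**5. What would a session baseline do to the estimates?** Let s be the shift in resting state left by the reset, in between-subject SD units. Assumptions, none from the article: s = 0, 0.5 or 1.0, the same for everyone; residual SD σ = 0.5; true change 0.30 with sound and 0.10 without; order balanced; baselines measured without error; no period term, as in Table 2.

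Each sound condition comes second for half the participants, so
- mean change = true change + s/2;
- sound contrast = (0.30 + s/2) − (0.10 + s/2) = 0.20;
- SD of the paired difference = √(2σ² + s²).

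| s | Mean change, sound / silent | Contrast | SD of difference |
|---|---|---|---|
| 0 | 0.30 / 0.10 | 0.20 | √0.50 = 0.71 |
| 0.5 | 0.55 / 0.35 | 0.20 | √0.75 = 0.87 |
| 1.0 | 0.80 / 0.60 | 0.20 | √1.50 = 1.22 |

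A simulation under the same assumptions gave the same means and contrast, and SDs of 0.71, 0.86 and 1.23. The variance of the paired difference rises by 0.75/0.50 = 1.5 times and 1.50/0.50 = 3 times. With a baseline before each condition the results stay at 0.30 / 0.10 and 0.71 for every s.

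**6. Limits of the illustration.** A constant shift could also be absorbed by a period term, which would restore the precision of the contrast but not correct the mean change. A real condition baseline has its own error: with SD τ, subtraction gives variance 2σ² + 2τ², so it improves the sound contrast only if s² exceeds 2τ². The firm gain is in the change from baseline.

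**7. Human versus digital.** Each session holds one first and one second condition, so the same s/2 enters both session means and cancels if the reset acts alike on both days.

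**The case against.** The best reply is that the Overview already states the intention and that repeating the procedure may be meant to include the rest recording. Recording does begin before the stimulus in every condition, signals are segmented relative to stimulus onset, and Fig. 1, which is not available here, may show a second baseline. This stands to the extent that the effect on the second condition depends on following the procedure as written. It does not remove the conflict: the interval before the stimulus is given neither a length nor a resting state, and the setup baseline lies outside the steps to be repeated.

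The reply is also right on several stronger readings that a reader might infer:

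- **One baseline per participant in the analysis.** The plural wording does not establish this. The level is simply not fixed.
- **Biased condition contrasts.** A session baseline cancels by subtraction from the sound contrast and so does nothing there to remove the reset effect. That is not bias, because order is randomized and counterbalanced.
- **Lighting left raised for the second condition.** The increase is confined to the reset, and the setup section asks for a consistent level. Only an after-effect is in question.
- **Percentage change applied to haemoglobin signals that are already changes.** The text allows subtraction or percentage change as appropriate and does not assign the latter to fNIRS.
- **A threat to the primary outcome.** KSS is rated at session start and again at the end of the reset, so a value exists before each condition.

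The Limitations section concedes that time-on-task, fatigue and repeated exposure cannot be excluded. It does not mention the reset or a baseline from before it.

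**Conclusion.** The point holds as an inconsistency in the recording procedure, with an unfixed baseline level in the analysis text. It is limited to secondary outcomes, which the article itself treats as complementary indicators. If one baseline per session is taken and used, one of the two conditions in each session (two of four per participant) is referenced to a state at least 30 min old and from before the reset. The mean physiological change from baseline is then off by half the after-effect of the reset. The size of that after-effect is unknown: 0.25 to 0.50 SD follows from an assumed 0.5 to 1.0 SD, and zero follows if it has worn off. The sound contrast keeps its expected value but loses precision under the listed model. Its unbiasedness assumes that order is balanced as planned and that the after-effect does not depend on which condition came first. The matter deserves correction before data collection because the resting reference stands in for a control condition and cannot be added later.

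**What to change.** 1. In Experimental procedure, add a five-minute fixation baseline immediately before each stimulus condition, under the standard session lighting. For the second condition it comes after the reset and its KSS rating. The existing setup recording can serve for the first condition.
2. In Data pre-processing, state that each condition is corrected with its own preceding baseline.
3. Check that the Overview, Equipment and environment setup, Experimental procedure and Fig. 1 agree with this.

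Using the baseline as a covariate, log scales for skewed measures, or a period term are optional analysis choices that this point does not require.

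Cost: about 5 min per session, taking the timed elements from 50 to 55 of about 70 min. The remaining 15 min must cover arrival, sensor fitting and removal, and the post-session questionnaires. The article does not time these steps, so the session length should be checked in a pilot run. No change to the design, the primary outcome or the model is needed.

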**Fig. 1 fig0001:**
[figure not shown]
Protocol overview showing three-phase structure with pre-experiment assessment, two experimental sessions, and post-experiment assessment.

### Participant selection and screening

Participants will be excluded if they meet any of the following criteria:•Self-reported diagnosed mental health disorders•Self-reported hearing impairments•Inability to tolerate wearable sensing devices or experimental procedures•Evidence of acute or chronic sleep deprivation, defined as insufficient sleep duration or extreme baseline sleepiness, identified during pre-session screening as described below.

To characterize sleep status and identify potential sleep deprivation prior to laboratory testing, a multi-tiered sleep assessment will be conducted. Wearable-based sleep monitoring will be conducted prior to the laboratory session. Participants who already use consumer smartwatches (e.g., Apple Watch, Fitbit, or Google Pixel Watch) will report their sleep timing data (bedtime and wake time) for the 3 nights preceding the application to participate in the study. For participants without a smartwatch, a Fitbit device will be provided to collect sleep timing and duration data for a minimum of 3 consecutive nights. Consumer-grade wearables have demonstrated reasonable accuracy, particularly for estimating total sleep duration, when compared with medical-grade devices [28,29]. In addition to wearable-based sleep tracking, baseline subjective sleepiness will be assessed before each laboratory session using the Karolinska Sleepiness Scale (KSS).

Participants meeting any of these criteria will be excluded to avoid potential confounding effects of acute or chronic sleep deprivation:•Average sleep duration is <5 h across monitored nights as measured by a smartwatch•Baseline KSS score ≥ 7

Sleep assessment will be conducted at the time of application, and only eligible participants will be notified and will subsequently be invited for pre-experiment assessment (see next section).

### Phase 1: pre-experiment assessment

Upon arrival, the participant will be provided with an overview of the study objectives and experimental procedures. They will be informed that the study examines responses to visual and audiovisual stimuli involving human and digital characters. To minimize expectation effects and participant demand characteristics, the specific focus on yawning stimuli will not be disclosed prior to stimulus presentation. The informed consent document will be reviewed in detail, and participants will be given the opportunity to ask questions before participation. Written informed consent will then be obtained prior to any data collection. Following consent, each participant will be assigned an anonymous identification code to ensure confidentiality throughout the study.

After the consent process, baseline questionnaire assessments will be administered to characterize individual sleep-related traits and personality factors. Circadian preference will be assessed using the Munich Chronotype Questionnaire (MCTQ), habitual sleep quality will be evaluated with the Pittsburgh Sleep Quality Index (PSQI), and personality traits will be measured using the Big Five Personality Test (BFPT). These measures will be collected to support descriptive characterization of the sample and to enable exploratory moderation analyses in subsequent data analysis.

Whenever possible, questionnaires will be provided in electronic format to facilitate efficient data entry and management. Participants will be instructed to complete the questionnaires at their own pace in a quiet and comfortable setting, with sufficient time allocated to minimize fatigue or response pressure.

### Phase 2: experimental sessions

The experimental phase consists of two intervention sessions conducted on separate days with a minimum one-day interval to minimize potential carryover effects related to fatigue or transient sleepiness. Each session corresponds to one stimulus type (human yawning vs. digital character yawning), with session order randomized across participants. Each session will follow an identical structure and last approximately 70 min. To minimize circadian confounding, experimental sessions will be scheduled at approximately the same time of day, typically between 14:00 and 16:00, consistent with prior findings that yawning exhibits circadian variation in both animals and humans [30,31]. The second session will be conducted within ±1–2 h of the first session whenever feasible. Sessions will be scheduled to avoid early morning or late evening when spontaneous yawning frequency is known to be naturally elevated [14,32,33].

#### Pre-session sleep quality and baseline sleepiness assessment

At the beginning of the session, participants will be greeted and their readiness to proceed will be confirmed. Sleep quality from the previous night, as measured by a smartwatch, will be reviewed. Baseline sleepiness will be assessed using the KSS. These data will be used to verify that the participant does not meet the exclusion criteria. Participants will then be instructed to observe the stimuli naturally without performing any explicit task. They will also be informed that they are free to yawn (or not) according to their natural inclination throughout the session, including during baseline recording.

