### Data collection and management

#### Data collection overview

Physiological data will be collected continuously during the experimental sessions using a multimodal sensing setup. Questionnaire data will be collected at multiple timepoints. Table 1 summarizes all data that will be collected and their corresponding instruments.

**Table 1 tbl0001:** Data collection summary.

Instruments	Data collected	Data collection timing
Consumer-grade smartwatches	Sleep duration, sleep schedule	Participants screening, and throughout the experiment days
KSS questionnaire	Baseline and post-condition subjective sleepiness levels	Participants screening, pre-experiment session baseline, post-condition, end of wakefulness reset period
MCTQ questionnaire	Chronotype	Pre-experiment assessment
PSQI questionnaire	Subjective sleep quality over the past one month	Pre-experiment assessment
Big Five Personality	Personality traits	Pre-experiment assessment
Research-grade smart wristband	Blood volume pulse (BVP), heart rate variability (HRV), electrodermal activity (EDA), 3-axis acceleration, and skin temperature	Experimental sessions
Eye-tracking system	Pupil diameter of both eyes	Experimental sessions
Functional near-infrared spectroscopy (fNIRS) system	Changes in HbO_2_ and HHb in the prefrontal cortical regions, head movements captured by 3-axis acceleration	Experimental sessions
Video recorder	Used solely to identify observable yawning behavior (counts of yawning, eye closure duration); recordings will be permanently deleted after feature extraction	Experimental sessions
Simple Likert Scales	Stimulus naturalness and comfort ratings	Experimental sessions
Semi-structured interview	Post-experiment interview responses	Post-experimental assessment

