Exploratory outcomes will include behavioral indicators of sleepiness, such as yawning occurrence and instances of sleep onset observed during the experiment. Additional exploratory analyses will examine the relationship between yawning behavior and both subjective and physiological outcomes. These relationships will be modeled using mixed-effect approaches where appropriate, which allows for the inclusion of both within-subjects (e.g., condition, time) and between-subjects (e.g., chronotype, baseline sleep quality) factors.

Statistical significance will be evaluated using two-sided tests with an alpha level of 0.05 unless otherwise specified. Results will be reported using effect sizes (e.g., estimated mean differences as quantified by Cohen’s *d* or Hedge’s *g*) alongside 95% confidence intervals and p-values. Given the exploratory nature of several outcomes, findings will be interpreted with appropriate caution, and emphasis will be placed on the direction, magnitude, and consistency of observed effects rather than statistical significance alone. The data analysis plan is summarized in Table 2.

**Table 2 tbl0002:** Data analysis plan.

Analysis Level	Procedure
Primary outcome analysis	▪ Analyze changes in KSS using linear mixed-effects models to account for the within-subject repeated-measures design ▪ Fixed effects will include stimulus type (human vs digital character yawning), auditory condition (with sound vs without sound), and their interaction. ▪ Subject will be included as a random effect with a random intercept to account for interindividual differences in baseline sleepiness. ▪ Where model convergence permits, random slopes for condition effects may be explored. ▪ Conduct planned comparison [50] to examine differences in subjective sleepiness between human and digital yawning stimuli, differences between auditory conditions (with vs without sound), and the interaction between stimulus type and auditory condition.
Secondary outcome analysis	▪ Apply the mixed-effects modeling framework used for primary outcome analysis to each physiological outcome, including HRV, EDA, skin temperature, pupil dynamics, and fNIRS measures. ▪ Analyses will focus on changes relative to baseline and associations with experimental conditions. ▪ Where appropriate, multiple comparison adjustments (e.g., Bonferroni or false discovery rate correction) will be reported as supplementary information.

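### Previous-night sleep is recorded for each session but left out of the stated KSS model, where it adds avoidable variance to the human-versus-digital contrast; the session-day sleep check also has no sleep criterion that fits it

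*Protocol article*

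**What the plan says.** **Eligibility.** Participant selection and screening gives two sleep-related exclusions: "Average sleep duration is <5 h across monitored nights as measured by a smartwatch" and "Baseline KSS score ≥ 7". Owners of a smartwatch "will report their sleep timing data (bedtime and wake time) for the 3 nights preceding the application to participate in the study"; the others wear a supplied device for at least 3 consecutive nights. On timing the section states: "Sleep assessment will be conducted at the time of application, and only eligible participants will be notified". It also has the KSS taken before each laboratory session.

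**Session day.** Pre-session sleep quality and baseline sleepiness assessment states: "Sleep quality from the previous night, as measured by a smartwatch, will be reviewed". The KSS is then taken, and both readings are to confirm that no exclusion criterion is met.

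**Data.** Table 1 lists sleep duration and schedule from consumer smartwatches, with timing "Participants screening, and throughout the experiment days".

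**Design.** Phase 2 ties each session to one stimulus type, on separate days, with session order randomised. Both sound conditions occur within each session.

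**Model.** Table 2, primary outcome: "Fixed effects will include stimulus type (human vs digital character yawning), auditory condition (with sound vs without sound), and their interaction", plus a random intercept for subject. Random slopes are optional. No term for previous-night sleep, session or period is listed.

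**The concern.** Stimulus type and test day coincide within each participant. Anything that makes one day sleepier than the other, prior sleep included, enters the participant's human-minus-digital difference in full. It cancels from the sound difference, which is taken within a day. The trial already holds a pre-stimulus measurement of one likely source of this variation, and the stated model does not use it. At stake is the precision of the human-versus-digital comparison, which answers the protocol's second research question.

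The eligibility text has a related gap. The session-day section says that a single night's sleep quality helps to verify the exclusion criteria, but the only sleep criterion is a mean duration over several nights, placed at application. Read literally, the previous-night reading has nothing to be judged against.

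**Working it through.** The protocol article gives no sample size, SD, effect size or power, so there is no stated figure to reproduce. Every size below rests on assumed inputs.

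**1. Where day-to-day variation goes.** Set the residual variance to 1 and the session-to-session variance to *k*. With 2 sessions and 2 sound conditions, the per-participant contrasts, scaled to residual variance 1, have these variances:
- stimulus (mean of human session minus mean of digital session): 1 + 2*k*
- sound: 1
- interaction: 1

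Only the stimulus contrast carries *k*.

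**2. Bias.** With randomised session order and no true effect, simulation (10,000 runs per scenario, assumed N = 20 and 40, *k* from 0 to 1) gave mean stimulus estimates between -0.004 and 0.007, that is, about zero.

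**3. Gain from the covariate.** Let ρ be the correlation between the session difference in previous-night sleep and the session difference in KSS. The share of contrast variance removed is ρ², and the equivalent gain in sample size is 1/(1 - ρ²) - 1.

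| ρ (assumed) | variance removed | equivalent sample gain |
|---|---|---|
| 0.1 | 1% | 1.0% |
| 0.2 | 4% | 4.2% |
| 0.3 | 9% | 9.9% |
| 0.4 | 16% | 19.0% |

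**4. Cost of estimating the slope.** Estimating one slope from N session differences inflates the variance by about (N - 2)/(N - 3): 18/17 = 1.059 at N = 20 and 38/37 = 1.027 at N = 40. The net variance ratio is (1 - ρ²)(N - 2)/(N - 3).

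| ρ | N = 20 | N = 40 |
|---|---|---|
| 0.1 | 1.048 | 1.017 |
| 0.2 | 1.016 | 0.986 |
| 0.3 | 0.964 | 0.935 |
| 0.4 | 0.889 | 0.863 |

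Break-even is at ρ² = 1/(N - 2): ρ of about 0.24 at N = 20 and 0.16 at N = 40. In a sample of 20, a correlation of 0.2 therefore gives no net gain.

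The simulation agrees. With sleep assumed to explain 30% of the session variance and *k* = 1, ρ² = 0.3 × 2/(1 + 2) = 0.20, slightly above the range in step 3. The SD of the contrast fell from 0.383 to 0.352 at N = 20 and from 0.275 to 0.248 at N = 40. With *k* = 0 it rose slightly, from 0.220 to 0.227 and from 0.159 to 0.161.

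**5. What the covariate does not fix.** A model with only a subject intercept pools the three contrast variances into (3 + 2*k*)/3 = 1 + 2*k*/3, whereas the stimulus contrast needs 1 + 2*k*. The large-sample type I error at nominal 0.05 is 2(1 - Φ(1.96/√[(1 + 2*k*)/(1 + 2*k*/3)])). If the covariate takes out 30% of *k*, then 0.7*k* remains.

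| *k* | stated model | covariate alone |
|---|---|---|
| 0.25 | 0.084 | 0.075 |
| 0.5 | 0.110 | 0.095 |
| 1 | 0.144 | 0.125 |

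In the simulations without the covariate, testing the stimulus contrast against its own between-participant variation, which is what a subject-by-session term does, gave 0.048 to 0.056 in every scenario.

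**6. If the outcome is change from session-start KSS.** An additive day effect cancels. The simulated SD of the contrast was then the same for every *k* (0.387 to 0.391 at N = 20), and adjusting for sleep only cost precision (0.397 to 0.400). The session term is still needed: the error in the shared baseline, assumed equal to the residual variance, gave a type I error of 0.142 to 0.148 without it.

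**7. Eligibility text side by side.**

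| session-day reading | criterion it could be judged against |
|---|---|
| KSS | 7 or more: same measure, and the KSS is repeated before each session |
| previous-night sleep quality | none: the sleep criterion concerns duration, averaged over several nights, assessed at application |

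**The case against.** - **The session day is not unscreened.** KSS of 7 or more is re-checked before each session, so a participant who is extremely sleepy on one day is caught that day. This stands. It does not cover someone who slept little but rates below 7, and the protocol lists short sleep as a separate ground for exclusion.
- **No bias.** A reader might infer that unequal sleep on the two days tilts the human-versus-digital result. The documents do not support that: session order is randomised and counterbalanced, so the harm is added variance.
- **Change scores absorb the day effect.** Data analysis names change relative to baseline, and a session-start KSS is collected. This stands in large part. The same section also names comparison across conditions and does not fix which KSS baseline is used, so the cancellation is not assured. Physiological outcomes are baseline-corrected, which weakens the case there; the covariate is therefore proposed for the KSS model only.
- **Precision covariates belong in an analysis plan that is not shown.** Fair as a general rule. Here the article itself lists the primary model's fixed effects, so improving that list is a legitimate comment, although the absence of the covariate is not an error.
- **The check might use experiment-day nights.** The criterion speaks of monitored nights, and Table 1 has the watches recording on experiment days. That reading is possible, but the statement that sleep is assessed at application points the other way. This is why the text needs reconciling.
- **Measurement error.** Sleep comes from mixed consumer devices, which will weaken ρ. This stands.

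**Conclusion.** The point holds as a modest opportunity for precision plus a mismatch in the eligibility text. Prior-sleep differences between days fall on the human-versus-digital contrast only, and the stated model leaves out a measurement that the trial already takes. On an assumed ρ of 0.2 to 0.4 the covariate removes 4% to 16% of the contrast variance before the cost of estimating it. The gain is at the low end or below under change from session-start KSS, and nil or slightly negative in a sample of about 20 when ρ is near 0.2. The documents supply none of ρ, N, *k* or the 30% share.

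Two stronger readings are not supported: that the contrast is biased, and that the sleep covariate would make its test valid. The standard error is a matter of the missing subject-by-session term. Nor does the text show that sleep-deprived participants go unscreened on the session day. It shows only that the KSS is the one session-day reading with a matching criterion.

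**What to change.** 1. **Primary KSS model.** Add previous-night sleep duration, centred within participant, as a session-level covariate, together with a random subject-by-session (equivalently subject-by-stimulus) term. Name the covariate in advance. If the outcome is change from session-start KSS, or that KSS is itself a covariate, the sleep covariate can reasonably be kept as a sensitivity analysis; the random term is needed either way.
2. **Eligibility text.** Reconcile Participant selection and screening with Pre-session sleep quality and baseline sleepiness assessment: state which session-day sleep measure is judged against which criterion. No threshold is proposed here; that choice belongs to the investigators.

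**Cost.** One covariate (one degree of freedom), one variance component, and a sentence or two of text. No new data collection, since Table 1 already lists sleep duration on the experiment days. The downsides are device measurement error and, in a small sample, a possible slight loss of precision.
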